**FIGURE 1 F1:**
[figure not shown]
Schematic representation of the tri-process model of interpersonal mindfulness.

This paper aims to present the tri-process model of interpersonal mindfulness, its theoretical and empirical foundations, and to describe a study protocol, which tests the model and explores its mechanisms of action. Interpersonal mindfulness will be grounded in interpersonal interactions, specifically in the influence exerted by an individual with mindfulness training on another person (a stranger) during dyadic interactions. We call the individual with training a Support-Provider or SP (as they will provide socioemotional support) and the other a Support-Receiver or SR (as they will receive support from the SP). To empirically test this model, we are proposing the use of a randomized-controlled trial that aims to compare the effects of mindfulness training (MT) to an active control (relaxation training, RT) on (1) the SP receiving the training, (2) their interpersonal interactions with a stranger in a lab setting, and (3) the individual interacting with them and the mechanisms behind these effects. In detail, we aim to examine the effects of the type of training (MT vs. RT) on self-awareness (measured by mindfulness disposition), self-regulation (measured by stress and emotional/cognitive regulation) and self-transcendence (measured by prosocial tendencies/behaviors such as empathy, compassion, active listening, and perspective taking) of the SP receiving the training and providing support (Objective O1.1) and the moderators of these effects (e.g., adherence and quality of daily practice) (Objective O1.2). In addition, we aim to examine the effects of the type of training of the SP on the quality of their interpersonal relationship during a 15-min videotaped dyadic interaction with a stranger (SR) to whom they will provide socioemotional support (Objective O2.1) and the mediators of these effects (e.g., self-awareness, regulation, and transcendence of the SP; Objective O2.2). Moreover, we aim to investigate the effects of the type of training of the SP on changes in (a) affective and (b) mindfulness states of the individual receiving the support (SR) (Objective O3.1) and the mediators and moderators of these effects (e.g., quality of the SP/SR dyadic interactions as mediator and SR’s fears of compassion from others as potential moderator) (Objective O3.2).

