### 1.3. Main hypotheses

The following are the principal hypotheses of the study, and the numbering of the hypotheses is linked to the numbering of the objectives (e.g., H1.1 designates the hypothesis linked to the objective O1.1, Hbase designates the hypothesis at baseline, i.e., before randomization and the experimental procedure).

(H1.1) (a) Measures pertaining to S-ART will be significantly higher in SPs who receive MT compared to those who receive RT and thus, at post-training and at follow-up. The only measure that we hypothesize to be equally lower for both groups (at both time points) is stress. (b) Within-groups effects (i.e., among the three time points) will be significant for all the outcomes for the MT group, and only for stress for RT.

(H1.2) (a) The effects of MT on S-ART measures will be moderated by the adherence of the SPs to the practice at both time points (i.e., post-training and follow-up). (b) The effects of RT on stress will be moderated by the SPs’ adherence to practice.

(H2.1) (a) Objective and subjective measures pertaining to the quality of the SP-SR interactions will be significantly higher in dyads with a SP who received MT compared to dyads with a SP who received RT at both time points (i.e., post-training and follow-up). (b) Within-groups effects (across time) will be only significant for the dyads with an SP who received MT.

(H2.2) The effects of MT of the SPs on the quality of SP-SR interactions (measured subjectively and objectively) will be mediated by the increase on S-ART of the SPs at both times points (i.e., post-training and follow-up).

(H3.1) SRs who interacted with SPs who received MT training will show significantly (a) higher positive emotional states, lower negative emotional states and (b) higher mindfulness states following their interaction compared to those who interacted with SPs who received RT and thus, at both time points (i.e., post-training and follow-up). (c) Within-groups effects will be only significant for the SR who interacted with an SP with MT training.

(H3.2) The effects of MT of the SP on the emotional and mindfulness states of the SR will be mediated by the increase in the quality of the SP-SR interaction and moderated by SRs’ Fears of Compassion from Others (i.e., higher fears of compassion will reduce the mediation effects) at both time points (i.e., post-training and follow-up).

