In addition, the effects of the training on the SPs’ interpersonal mindfulness skills will be assessed using our recently developed and validated measure of interpersonal mindfulness, Interpersonal Mindfulness Questionnaire (IMQ; Khoury et al., 2022), which is based on Varela’s work (Varela et al., 1991, 2016) and the theory of embodiment (Khoury et al., 2017, 2019, 2020; Khoury, 2018) and include four sets of global trainable skills (detachment from automatic thoughts, body anchored presence, attention to and awareness of the other person, and empathic responding; Khoury et al., 2023). These skills were shown to highly relate to interpersonal functioning and were sensitive to meditation practice or mindfulness training (Khoury et al., 2022).

Daily logs will be used to measure adherence to and quality of home practice (during the 8-week training and the 3 months follow-up). In order to reduce the time for participants and increase feasibility, we will use the short forms (SF) of the scales when available (e.g., CERQ-SF; Garnefski and Kraaij, 2006; DERS-SF; Kaufman et al., 2016).

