Outcome (variable)	Variable type	Dyadic interaction Part I, III and IV of the experiment				Mindfulness/Relaxation training Part II of the experiment			
		Pre-induction	Post-induction	During interaction	Post-interaction	Pre-training	During training	Post-training	3-months follow-up
Trait mindfulness	Dep/Cntrl					SP		SP	SP
Perceived stress	Dependent					SP		SP	SP
Emotional regulation	Dependent					SP		SP	SP
Empathy	Dependent					SP		SP	SP
Compassion–Others	Dependent					SP		SP	SP
Active listening	Dependent					SP		SP	SP
Perspective taking	Dependent					SP		SP	SP
Interpersonal mindfulness	Dependent					SP		SP	SP
Behavior observation	Dependent			SP-SR					
Enacted social Support	Dependent				SR				
Adherence to practice	Control						SP		
Emotional experience	Cntrl/Dep.	SR	SR		SR				
State mindfulness	Dependent	SR	SR		SR				
Fears of compassion	Control	SR							
Social desirability	Control	SR				SP			

Dep, dependent; Cntrl, control; SP, support provider; SR, support receiver.

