#### 2.5.2. Experiment–Part II; mindfulness/relaxation training

SPs (total of 160) will be asked to complete measures of mindfulness, perceived stress, emotion regulation, empathy, compassion for others, active listening, perspective taking and interpersonal mindfulness. Then, they will be randomly and equally divided into two groups using a computer algorithm to ensure randomization and concealment. Half of the SPs (80) will receive the MT (MBSR-ld) and the other half will receive the RT. Participants in both groups will be asked to complete the daily logs during the 8 weeks. After the training, the same measures will be administered to the SPs.

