## 3. Data analyses strategies

To ensure data reliability, self-reported data will be inspected for normality and skewness and outliers will be eliminated. Interrater reliability for the behavior observation data will be computed. An interrater coefficient of 0.95 or above is expected.

To test H1.1, H2.1, and H3.1, we will perform a mixed (2 groups × 3 time-points) multivariate analysis of covariance (MANCOVA) controlling for social desirability (and for Fears of Compassion from Others for H3.1). MANOVA/MANCOVA allow to reduce Type-I errors (i.e., rejecting the null-hypothesis when it is true, correcting therefore for multiple comparisons) when testing changes in multiple dependent variables. To test H1.2, we will use a regression analysis. To test H2.2 and H3.2, we will use a path analysis. To test associations and meditation/moderation at baseline (Hbase), we will use correlations and PROCESS macro with 5,000 bootstrapped/bias-corrected confidence intervals (Hayes, 2018). Structural Equation Modeling (Klem, 2000) may be used as well if the power is sufficient.

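### The article gives two different windows for the practice logs, and H1.2 treats adherence measured after randomisation as a moderator when the planned regression can show only a within-arm association

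*Protocol article*

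**What the plan says.** **Hypothesis.** Objective O1.2 (Introduction, paragraph after Figure 1) concerns "the moderators of these effects (e.g., adherence and quality of daily practice) (Objective O1.2"). H1.2(a) in section 1.3 says the effects of mindfulness training (MT) on the S-ART measures "will be moderated by the adherence of the SPs to the practice at both time points (i.e., post-training and follow-up"). H1.2(b) says "The effects of RT on stress will be moderated by the SPs’ adherence to practice" and names no time point. RT is the relaxation arm.

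**Analysis.** Section 3: "To test H1.2, we will use a regression analysis". The model is not described further.

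**Collection of adherence.** Section 2.4 plans the logs "during the 8-week training and the 3 months follow-up". Section 2.5.2 says "Participants in both groups will be asked to complete the daily logs during the 8 weeks". In Table 1 the row "Adherence to practice" carries one SP entry, under the training column, and its variable type is Control. Section 2.5.4 names the SP follow-up measures one by one, and logs are not among them.

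**Timing.** Section 2.5.2 places randomisation of the SPs after the pre-training measures and before training, so every log entry is made after randomisation.

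**The concern.** There are two separate issues.

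The first is data collection. Two places give different end dates for the logs, and the places that research staff would work from (the schedule table and the procedure steps) show the shorter window. Daily practice cannot credibly be reconstructed months later; section 4 already concedes that participants forget. Section 2.6 runs one cohort per year, so each cohort handled on the shorter schedule loses its follow-up practice data for good.

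The second is interpretation. People choose how much they practise. Section 2.2.2 itself links adherence to motivation, giving about 85% for standard MBSR in highly motivated participants and 70% in students. The logs also record meditation in one arm and relaxation in the other. Comparing high and low adherers within an arm compares self-selected people, and randomisation gives no protection. A motivation effect could be reported as practice moderating the benefit of MT.

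**Working it through.** **A. Log window, place by place**

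| Place | Window |
|---|---|
| Section 2.4 | 8-week training plus 3-month follow-up |
| Section 2.5.2 (Part II) | 8 weeks |
| Table 1, adherence row | training column only; 3-month column empty, although it is filled for all eight SP self-report outcomes |
| Section 2.5.4 (Part IV) | logs not mentioned |

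Taking 3 months as about 13 weeks, the full window is 8 + 13 = 21 weeks. On the shorter schedule 13/21, or about 62%, of the practice period goes unrecorded. What remains for H1.2(a) at follow-up is adherence over the 8 weeks.

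**B. The plan's own figure**

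Sections 2.1 and 2.5.2 give a moderate effect, power 0.8, alpha 0.05, 15 to 20% attrition and 80 SPs per arm. Reading moderate as d = 0.5 and the test as two-sided (both assumptions):

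- n per arm = 2 × (1.96 + 0.84)² / 0.5² = 63, or 64 with the t distribution.
- At 20% attrition: 63/0.8 = 79 and 64/0.8 = 80.

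The 80 per arm reproduces, with about 64 completers. Both sizes are used below.

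**C. How large a spurious association could be**

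Assume practice has no effect and a stable trait such as motivation correlates 0.4 to 0.5 with both adherence and outcome. The documents give no such values.

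*Within-arm regression, unadjusted.* The spurious correlation is 0.4² = 0.16 to 0.5² = 0.25. The chance of p < 0.05 is approximately Φ(√(n − 3) × atanh r − 1.96):

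- n = 64: 7.81 × 0.161 = 1.26, giving 24%; 7.81 × 0.255 = 1.99, giving 51%.
- n = 80: 29% and 61%.

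A simulation at 80 per arm (4,000 runs, trait correlations 0.5) also gave 61% within MT.

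*Within-arm, adjusted for baseline.* Assume a baseline–outcome correlation of 0.6 and the trait equally related to both:

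- (0.16 − 0.16 × 0.6) / √[(1 − 0.16²)(1 − 0.6²)] = 0.064/0.790 = 0.08
- (0.25 − 0.25 × 0.6) / √[(1 − 0.25²)(1 − 0.6²)] = 0.100/0.775 = 0.13

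At n = 64 these are significant in about 10% and 17% of trials.

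*Change from baseline.* Under the same equality the covariance of adherence with change is 0.25 − 0.25 = 0, so there is no inflation.

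*Arm-by-adherence interaction* (simulated, 80 per arm, true d = 0.5 for everyone):

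| Trait–adherence correlation, MT / RT | Trait–outcome correlation | False rejection |
|---|---|---|
| 0.5 / 0.5 | 0.5 | 5.2% |
| 0.6 / 0.3 | 0.5 | 15% |
| 0.5 / 0 | 0.4 | 23% |
| 0.7 / 0.2 | 0.5 | 36% |

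The interaction test keeps its level when selection is equal in both arms and loses it when selection differs.

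**The case against.** **On the logs.** A reader might infer that the plan never collects follow-up adherence and that the follow-up half of H1.2 is therefore untestable. The documents do not support either step. Section 2.4 expressly plans logs through follow-up. Section 2.5.2 describes the 8-week training, so naming 8 weeks there is natural. Table 1 has no column for the interval between post-training and follow-up, where a diary would sit, and Part IV lists questionnaires given at a visit. The two time points in H1.2(a) may also refer to when the effects are measured, with 8-week adherence as the predictor, and that remains testable. All of this is fair. What stands is that the article gives two windows and never says which one goes with which time point.

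**On the regression.** A reader might take 24 to 51% as the expected rate of false findings. That holds only for an unadjusted within-arm regression under assumed correlations. Section 3 does not fix the model, and a condensed article may leave it to the analysis plan. Sections 2.3 and 3, on dyad power, speak of effects as changes between time points, and baseline values are collected. This narrows the size considerably. It does not remove the problem: using change cancels only a trait whose link with the outcome is the same before and after training. A trait that governs how much people gain remains. Calling the result moderation is wrong under any of these models.

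**On a causal remedy.** Someone might propose a complier-average effect with randomisation as instrument. It would require that assignment act on the outcome only through practising MT. The comparator is an active training with its own home practice (section 2.2.3), and H1.1 expects it to lower stress equally, so that restriction is not credible. For H1.2(b) there is no untreated arm.

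**Conclusion.** The concern holds in two limited parts.

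1. The article contradicts itself on how long adherence is recorded. If the table and procedure are followed, practice over the 3-month follow-up is not recorded, and H1.2(a) at follow-up has only 8-week adherence to work with. This part rests on the text alone.
2. The H1.2 regression estimates a within-arm dose-response association. It cannot show that adherence moderates the randomised effect of MT or RT. The size of any spurious finding is uncertain: roughly 5% to 60% false rejection for trait correlations of 0.4 to 0.5, with the low end for an interaction test under equal selection, 10 to 17% with baseline adjustment, and the high end for an unadjusted within-arm fit. Stronger assumed selection into practice in MT (0.6 or 0.7) pushed the unadjusted within-MT fit to 78% and 90% in the same simulation, so 60% is not a ceiling.

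The randomised comparisons in H1.1 are not affected.

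**What to change.** - **Log window.** Reconcile sections 2.4, 2.5.2 and 2.5.4 and Table 1. The simpler route is to extend the daily logs through follow-up in Table 1 and in the procedure, as section 2.4 already plans. If the logs are meant to stop at 8 weeks, correct section 2.4 instead. Settle this before a further cohort is run.
- **Window per time point.** State in H1.2 which adherence period goes with post-training and which with follow-up. If logs stop at 8 weeks, say that 8-week adherence is used for both; the follow-up hypothesis need not be dropped. Give H1.2(b) a time point as well.
- **Claim and model.** Reword H1.2 and its conclusion as a within-arm dose-response association, adjusted for the outcome's baseline value and for social desirability. Both are already collected from SPs before training.
- **Table 1.** Change the Control label for adherence so that it matches its role in H1.2.

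The cost is a few table and text corrections, no new instrument, and a more modest H1.2 claim. Logging through follow-up adds no burden beyond what section 2.4 already commits to.

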#### 2.5.3. Experiment–Part III; post-training

This part will take place after the end of the training and is similar to Part I, the only difference is that SR1 will be replaced by SR2 in the dyads. In addition, only the SR will complete the consent form and provide socio-demo/social desirability data, as SPs already did that in Part I.

#### 2.5.4. Experiment–Part IV; follow-up

This part takes place 3 months after the end of the training and is similar to Part III (with the only difference being that SR2 will be replaced by SR3 in the dyads). SPs will be asked to complete the same measures (mindfulness disposition, perceived stress, emotion regulation, empathy, compassion to others, active empathic listening, perspective taking, and interpersonal mindfulness skills). At the end of the experiment, both SPs and SRs will be debriefed about the study and its objectives.

### 2.6. Timeline

The recruitment of participants will be divided into four cohorts (one cohort per year of 160, 40 SPs, and 120 SRs). The four parts of the experiment (i.e., Part-I, Part-II, Part-III, and Part-IV), will be repeated for each of the four cohorts. During each year (four in total), 40 SPs will be receiving training [MT(20), RT(20)]. The SPs receiving MBSR or RT will be divided into groups of 6 to 8 participants, and, a total of six groups will be conducted each year. We will conduct two groups (one MBSR, one RT) simultaneously during the fall, winter, and summer academic semesters of each year.

## 3. Data analyses strategies

To ensure data reliability, self-reported data will be inspected for normality and skewness and outliers will be eliminated. Interrater reliability for the behavior observation data will be computed. An interrater coefficient of 0.95 or above is expected.

To test H1.1, H2.1, and H3.1, we will perform a mixed (2 groups × 3 time-points) multivariate analysis of covariance (MANCOVA) controlling for social desirability (and for Fears of Compassion from Others for H3.1). MANOVA/MANCOVA allow to reduce Type-I errors (i.e., rejecting the null-hypothesis when it is true, correcting therefore for multiple comparisons) when testing changes in multiple dependent variables. To test H1.2, we will use a regression analysis. To test H2.2 and H3.2, we will use a path analysis. To test associations and meditation/moderation at baseline (Hbase), we will use correlations and PROCESS macro with 5,000 bootstrapped/bias-corrected confidence intervals (Hayes, 2018). Structural Equation Modeling (Klem, 2000) may be used as well if the power is sufficient.

Regarding the dyadic data, we will use the Actor-Partner-Interdependence-Model (APIM; Kenny and Judd, 1986; Kenny and Malloy, 1988; Griffin and Gonzalez, 1995; Kenny, 1996; Kenny et al., 2020) and APIM-M (M for mediation) as we cannot assume independence between the members of the dyad (Gonzalez and Griffin, 2012). APIM/M allows us to test the interactions between the SP and the SR scores on a given predictor (Kenny et al., 2020). To calculate power for the APIM/M, we used a Monte Carlo simulation (Schoemann et al., 2014), which is applicable for APIM/M (Ledermann et al., 2022). Results suggested that 80 dyads per group should be sufficient (powered enough) to detect moderate effects (i.e., changes between baseline, post, and follow-up time points) for an alpha of 0.05. In addition, if for some dependent variables, the power is insufficient to detect a change, we will use Bayesian Analysis (Fitzpatrick et al., 2016) instead of APIM/M as authors have previously recommended (Sagan and Kowalska-Musiał, 2009; Ledermann et al., 2022). All the statistical analyses will be conducted using R (R Core Team, 2021). If multiple statistical analyses (e.g., *post hoc* ANOVAs or *t*-tests) are to be conducted sequentially on the same set of dependent variables, the level of significance (alpha) will be divided by the number of tests (multiple comparisons correction) to reduce the risk of false positives (i.e., reducing Type-I errors).

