## 2. Methods and design

### 2.1. Participants

We aim to recruit 640 adult community members (18–35 years old, 50% female) through advertising on social media. The sample size was based on detecting significant differences among the groups (i.e., between SPs with MT vs. SPs with RT), assuming a moderate effect (Khoury et al., 2013a,^2015^), a power of 0.8 and an alpha of 0.05 (Cohen, 1977) and the expectation 15 to 20% attrition rate. We will exclude participants who: (1) have a regular meditation practice; (2) have already participated in a formal mindfulness training (such as MBSR or a meditation retreat); or (3) had a social support skills training (e.g., counselors, psychologists, social workers, or other medical personnel).

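### Outliers in the self-reported outcomes will be deleted on distributional grounds, which removes valid scores after randomisation and can bias the comparison; type I error rises only if screening is done within arm

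*Protocol article*

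**What the plan says.** Section 3 (Data analyses strategies) opens with the purpose, "To ensure data reliability", and then the rule: "self-reported data will be inspected for normality and skewness and outliers will be eliminated". The article gives no cut-off. It does not say whether values are screened within arm or on the pooled sample, or whether the person screening is blind to allocation. It does not restrict removal to impossible or proven erroneous values, and it mentions no analysis with all data retained. No other section qualifies the rule.

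By its wording the rule covers self-reported data. According to section 2.4 and Table 1 these are the support provider (SP) scales, the support score rated by the support receiver (SR), the PANAS and the MAAS-State. The breath counting task and the BOMDI coding are not self-reported and fall outside it.

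The screened data then enter the 2 × 3 MANCOVA for H1.1, H2.1 and H3.1, the regression for H1.2 and the path analyses for H2.2 and H3.2.

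**The concern.** After their baseline measures, section 2.5.2 says of the SPs that "they will be randomly and equally divided into two groups using a computer algorithm to ensure randomization and concealment". Post-training and follow-up scores are therefore outcomes of a randomised comparison. Removing some of them because of their value makes membership of the analysed set depend on the outcome, and randomisation no longer protects the comparison.

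The design gives good reasons to expect genuine extreme scores. The mood induction in section 2.2.1 asks SRs to recall an event that caused intense negative emotion, so very high negative affect is a possible result of the procedure. H1.2 predicts that training effects vary with adherence, so unusually strong responders among the SPs would be part of the hypothesised signal. On a bounded questionnaire, a score at the edge of the range is still a valid score.

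At stake are the size of the estimated effect on most outcomes of the main hypotheses and, under one way of applying the rule, the false-positive rate.

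**Working it through.** **Inputs from the article.** Section 2.1 gives "a power of 0.8 and an alpha of 0.05", "assuming a moderate effect" and "the expectation 15 to 20% attrition rate". Section 2.5.2 gives the arm size: "Half of the SPs (80) will receive the MT (MBSR-ld) and the other half will receive the RT".

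**Assumptions, because the article gives no figures.** Moderate effect = 0.50 SD; two-sided test; outlier cut-offs |z|>3, |z|>2.5, |z|>2, the boxplot rule (1.5 × IQR) and 2.5 scaled median absolute deviations (MAD); data normal, t with 5 df, gamma (shape 2) or lognormal (sigma 0.5), all scaled to SD 1. A two-sample t-test stands in for the MANCOVA.

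**Step 1: reproduce the plan's size.** n per arm = 2 × (1.96 + 0.8416)² / 0.50² = 62.8, so 63, or 64 with the t correction. Allowing for 20% attrition, 64 / 0.80 = 80. At 15%, 64 / 0.85 = 75.3, so 76. The stated 80 per arm reproduces at 0.50 SD and 20% attrition. It contains no further allowance for deleted scores.

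**Step 2: no deletion, 64 per arm.** In 20,000 simulated trials per setting, type I error is about 0.05 for all four distributions, the mean estimate is 0.50 and power is about 0.80.

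**Step 3: deletion on the pooled sample.** Type I error stays at about 0.05 (0.048–0.054) in every setting. The harm is in the estimate. Results for normal data with a true effect of 0.50:

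| Cut-off | Mean estimate | Power |
|---|---|---|
| none | 0.50 | 0.80 |
| \|z\|>3 | 0.49 | 0.79 |
| boxplot | 0.47 | 0.77 |
| \|z\|>2.5 | 0.46 | 0.76 |
| \|z\|>2 | 0.40 | 0.69 |

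With skewed data the estimate is 0.44–0.48. Power there does not fall (it rises above 0.80, because the variance is trimmed too), but the estimate is biased.

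**Step 4: pooled deletion when the effect sits in a minority.** Suppose 15% of the mindfulness arm gain 0.50 / 0.15 = 3.33 SD and the rest gain nothing, so the mean effect is again 0.50. The estimate becomes 0.39 (|z|>3), 0.27 (|z|>2.5), 0.17 (boxplot) or 0.14 (|z|>2). If 10% gain 3 SD (mean effect 0.10 × 3 = 0.30), it becomes 0.22, 0.14, 0.11 or 0.07.

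**Step 5: deletion within each arm.** Type I error at nominal 0.05:

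| Data | \|z\|>3 | \|z\|>2.5 | \|z\|>2 | boxplot | MAD |
|---|---|---|---|---|---|
| normal | 0.06 | 0.07 | 0.11 | 0.07 | 0.08–0.09 |
| gamma | 0.08 | 0.09 | 0.11 | 0.14 | 0.17 |
| lognormal | 0.08 | 0.09 | 0.10 | 0.13–0.14 | 0.16 |

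For t with 5 df the range is 0.06–0.09. Trimming each arm around its own centre shrinks the residual variance that the test uses, while the arm means still differ by about as much as before, or more when the data are skewed.

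**The case against.** The strongest reply has four parts.

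*The test need not become anti-conservative.* A reader might infer from the sentence that the tests as such become anti-conservative. The article does not support that: inflation needs screening within arm, and the article speaks only of inspecting self-reported data, with no mention of group. Pooled screening holds type I error at about 5%. This part stands.

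*The size depends on assumed data and cut-offs.* The strong-responder patterns in step 4 are illustrations; the article describes none. The upper end of the within-arm inflation comes from unbounded skewed distributions, whereas these scales are bounded. On simulated sums of ten 5-point items, within-arm deletion gives 5.4–6.7% at 3 SD and 6.6–9.9% with the boxplot rule; a 2 SD cut-off gives 10–11%. More extreme figures from heavier-tailed unbounded data should not be quoted for this trial. For an ordinary 0.50 SD shift and a pooled 3 SD rule the loss is trivial. This also stands, and it is why the result is given as a range.

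*The loss of participants is not fixed.* A reader might infer that one deleted score removes an SP from every outcome and time point. The article does not say so. With 8 SP measures × 3 times = 24 independent normal scores, the boxplot rule would flag at least one score in 1 − (1 − 0.0070)²⁴ = 15.5% of SPs, but related scales repeated on one person are correlated, which lowers that share. It cannot apply in that form to the SR outcomes, because the three SRs matched to an SP are different people.

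*A condensed article may leave the definition to an analysis plan.* It may, and the missing cut-off is not the point. The article also gives data reliability as the purpose, and screening may in practice be blind. But the elimination itself is fixed here without condition, and no definition of an outlier short of restricting it to errors would keep valid scores in the analysis.

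**Conclusion.** The point holds in a limited form. The plan commits to removing self-reported outcome values because of where they lie in the observed distribution, with no limit to errors. That makes the analysed set depend on the outcome and can bias the randomised comparison.

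The size is conditional on what the article leaves open. With pooled screening the false-positive rate is intact and a true 0.50 SD effect shrinks to about 0.40–0.49 for normal data, or to 0.14–0.39 if 15% of the mindfulness arm carry the whole effect. With within-arm screening type I error is about 5–11% for normal data and about 8–17% for skewed data. These figures rest on 64 per arm, the assumed cut-offs and distributions, and a t-test in place of the MANCOVA. They do not show that the trial's tests will be anti-conservative, nor that a given share of SPs will be lost. The behavioural outcomes (breath counting and BOMDI) are unaffected.

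**What to change.** Replace the outlier clause in section 3 by: *All valid scores are analysed. Only values impossible for the scale or proven recording errors are corrected or set to missing, without knowledge of arm. Skewness is handled by transformation or by robust or bootstrap inference. Any analysis without outliers is a sensitivity analysis only.*

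If such a sensitivity analysis is kept, its cut-off and screening unit should be fixed before the data are examined. In the simulations, keeping all scores gave about 5% type I error, about 80% power and an unbiased 0.50. The cost is one sentence in the plan and a little more analysis work. The design and the sample size do not change.

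### For H1.1(a), the 2 × 3 MANCOVA uses the support provider's pre-randomisation score only as an outcome level, so the MT–RT comparison is valid but less efficient than the collected data allow

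*Protocol article*

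**What the plan says.** Section 3 (Data analyses strategies) names one model for H1.1, H2.1 and H3.1: "we will perform a mixed (2 groups × 3 time-points) multivariate analysis of covariance (MANCOVA) controlling for social desirability". Fears of Compassion from Others is added as a covariate for H3.1 only, so social desirability is the only covariate for H1.1.

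Section 1.3 splits H1.1 into two parts.
- Part (a) is between groups: "Measures pertaining to S-ART will be significantly higher in SPs who receive MT compared to those who receive RT and thus, at post-training". The same is predicted for the follow-up visit. Stress is the exception and is predicted to fall equally in both arms.
- Part (b) is within groups: "Within-groups effects (i.e., among the three time points) will be significant for all the outcomes for the MT group". In the RT group the prediction covers stress alone.

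Table 1 places the SP measures at pre-training, post-training and the 3-month follow-up. Section 2.5.2 fixes the order. The scales come first: "SPs (total of 160) will be asked to complete measures of mindfulness, perceived stress, emotion regulation, empathy, compassion for others, active listening, perspective taking". Interpersonal mindfulness is measured on the same occasion. The allocation to training follows: "Then, they will be randomly and equally divided into two groups using a computer algorithm to ensure randomization and concealment". The pre-training scores therefore precede the allocation to MT or RT.

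Section 2.1 sizes the trial on the difference between the two SP groups, "assuming a moderate effect", with power 0.8, alpha 0.05 and 15 to 20% attrition. It mentions no correlation between repeated scores.

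**The concern.** H1.1(a) asks whether MT and RT differ at two visits after randomisation. Each SP also has a score on the same scale from before randomisation, which predicts the later scores and cannot be affected by the training. Using that score as a covariate removes the part of the later variance that it explains. In the planned layout it is instead one of three outcome levels. The group × time term then compares raw changes, so each SP's full baseline noise is carried into the contrast.

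What is at stake is precision on the first link of the tri-process model, the effect of training on the SP. The information is already collected and the planned model leaves part of it unused. Bias and type I error are not at issue.

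**Working it through.** **Inputs from the article:** 80 SPs per arm (section 2.5.2); power 0.8, alpha 0.05, attrition 15 to 20% and a moderate effect (section 2.1).

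**Assumptions, not in the article:** moderate means d = 0.5, the same at post-training and follow-up; two-sided test; SD 1 at each visit; equal correlation rho between any two visits (compound symmetry); one outcome at a time.

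**1. The plan's own size.** An unadjusted two-sample t-test with d = 0.5 needs 64 per arm for power 0.80 (exact value 0.801). With 20% attrition, 64 / 0.80 = 80 per arm, or 160 SPs. Four groups of 160 make 640. The stated size matches a two-group comparison without baseline adjustment.

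**2. Two-df comparison over both later visits, n = 64 per arm.**
- Planned group × time term: noncentrality = (n/2)(2d²/3)/(1 − rho) = 32 × 0.1667/(1 − rho) = 5.33/(1 − rho), on 2 and 252 df.
- Joint test of both later visits, adjusted for baseline: noncentrality = (n/2) × 2d²/[(1 − rho)(1 + 2 rho)] = 16/[(1 − rho)(1 + 2 rho)], on 2 and 124 df.

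| rho | noncentrality, planned | noncentrality, adjusted | power, planned | power, adjusted |
|---|---|---|---|---|
| 0.3 | 7.62 | 14.29 | 0.69 | 0.93 |
| 0.5 | 10.67 | 16.00 | 0.84 | 0.95 |
| 0.7 | 17.78 | 22.22 | 0.97 | 0.99 |
| 0.8 | 26.67 | 30.77 | 0.998 | 0.999 |

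The ratio of the two noncentralities is 3/(1 + 2 rho): 1.88 at rho 0.3, 1.50 at 0.5 and 1.15 at 0.8. It exceeds 1 for every rho below 1. A simulation of 4,000 trials at rho 0.5 gave 0.83 for the group × time test in its multivariate form, against 0.832 calculated for that form.

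**3. Single-visit comparison.** A change score has variance 2(1 − rho) and a baseline-adjusted score 1 − rho². The noncentrality is (n/2)d² = 8 divided by that variance.

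| rho | variance, change | variance, adjusted | power, change | power, adjusted |
|---|---|---|---|---|
| 0.3 | 1.40 | 0.91 | 0.66 | 0.84 |
| 0.5 | 1.00 | 0.75 | 0.80 | 0.90 |
| 0.7 | 0.60 | 0.51 | 0.95 | 0.98 |

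**4. With alpha divided over the two visits (0.025 each), as section 3 asks of sequential tests.** An unadjusted t-test at one visit has power 0.71. The change score has 0.55, 0.71 and 0.92 at rho 0.3, 0.5 and 0.7. The adjusted contrast has 0.76, 0.84 and 0.95. Dividing over more tests lowers all of these.

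**5. Where the planned group × time term reaches 0.80.** This happens at rho of about 0.45 with 64 per arm (20% attrition) and about 0.42 with 68 per arm (15%).

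**The case against.** The strongest defence is that the 2 × 3 layout has a purpose. H1.1(b) concerns change across three time points within each arm, and for stress the prediction is an equal fall in both arms. Both need the pre-training visit among the outcomes. This stands: dropping that visit altogether would leave H1.1(b) without a test.

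A reader might infer that the trial misses its power target, because a group main effect averaged over all three levels is diluted by a baseline level where the true difference is zero (power 0.63 at rho 0.5). The article does not support that inference. It never names the group main effect as the test of H1.1, and it describes the method as one for testing changes, which points to group × time. That term reaches 0.8 or more once rho is about 0.45, and no rho is stated.

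It is also fair that a standard MANCOVA applies the same covariates to every outcome. Adjusting each measure for its own baseline therefore takes a model per outcome, which costs more than a change of wording. The power figures are for one outcome. Multivariate power depends on correlations between scales that the article does not give.

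Table 1 does label trait mindfulness as both dependent and control. That is one measure only, and section 3 does not carry it into the H1.1 model. The remaining point is narrow: the model is stated explicitly, its H1.1 covariate list omits the SP's own baseline, and adjustment is at least as precise at every rho.

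**Conclusion.** The point holds as a matter of efficiency for the between-group test of H1.1(a). The planned comparison is a valid randomised comparison, but it does not use the pre-randomisation score for adjustment. Under the assumptions above, the like-for-like loss is about 24 power points at rho 0.3 (0.93 − 0.69), 11 to 12 at 0.5, 2 at 0.7 and almost none at 0.8. At a single visit, adjustment gains about 18, 10 and 2 points over change scores at rho 0.3, 0.5 and 0.7. Because rho is unknown, the size of the loss is a range, and failure to reach the stated 0.8 is not established.

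The point is confined to SP scores. In H2.1 and H3.1 a different support receiver is seen at each visit, so the receivers' own ratings and states have no earlier score from the same person at a previous visit to adjust for in this way.

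**What to change.** Keep the three-time-point analysis for the within-group effects of H1.1(b).

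For H1.1(a), state that the MT–RT difference will be tested at post-training and at follow-up for each S-ART measure, adjusted for the SP's own pre-training score on that measure and for social desirability. A repeated-measures model with baseline means constrained equal across arms would also serve and retains all three visits. Apply the alpha division of section 3 across these tests and state how many tests it covers. For stress, report the adjusted difference in the knowledge that H1.1(a) predicts none.

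The cost is a small amount of extra analysis: per-outcome models beside, or in place of, the omnibus MANCOVA for H1.1(a), with the multiplicity control moving to the divided alpha if the omnibus test is dropped. No new participants, visits or measures are needed.
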